### Positive coping

A range of positive coping measures will also be collected as secondary outcomes. Mental wellbeing will be evaluated using the short *Warwick*-*Edinburgh Mental Well*-*being Scale* (SWEMWBS) [26, 27]. The SWEMWBS is a self-report scale that consists of seven positively worded items that measure different aspects of positive mental health. Each item is rated on a five-point Likert type scale ranging from 1 (none of the time) to 5 (all of the time), with a total scale score (7–35) calculated by transforming and then summing item scores, with higher scores indicating a greater level of mental wellbeing.

A further eight-item scale, drawn from the previous US Sources of Strength evaluation [10], will be included to specifically assess *Sources of Strength Coping*. These items measure the extent to which students view the eight resources targeted by the Sources of Strength program as useful to them in overcoming challenges in their life. These resources cover both formal (e.g. access to mental health) and informal resources (e.g. family). Items on this scale are responded to on a four-point scale ranging from 1 (strongly disagree) to 4 (strongly agree), with higher scores indicating greater coping.

Social support will additionally be measured using the supportive interactions and negative interactions questions from *Schuster*’*s Social Support Scale* [28]. Fifteen items will be used to measure both positive and negative interactions with friends, family members, and teachers (in place of the original ‘spouse’ category), rated on four-point Likert scale ranging from ‘often’ to ‘never’. Scores are interpreted per category, for friends, family members, and teachers. Higher scores on the supportive interactions scales are indicative of more supportive interactions, and higher scores on the negative interactions scales indicate more negative interactions.

Coping mastery, or the belief that life is under an individual’s control rather than fatalistically determined, will also be assessed using the seven-item *Pearlin Mastery Scale* [29]. Items on this scale are rated on a four-point scale ranging from 1 (strongly disagree) to 4 (strongly agree). Negatively worded items require reverse coding prior to scoring, with higher scores indicating greater levels of mastery.

### Suicidality

Suicidality is a key secondary outcome, as one of the long-term goals of the Sources of Strength program is to prevent and reduce suicidal thoughts and behaviours, after the cessation of the program, through the promotion of help-seeking and positive coping. The *Youth Risk Behaviour Survey* (YRBS) [30] is a four-item (yes/no) measure that will be administered to assess if the respondent has had suicidal ideation or made a suicide plan or attempt (and its seriousness) during the past 12 months. Research indicates that the measurement of suicidal behaviours in adolescents is acceptable and does not pose an iatrogenic risk [31, 32]. Suicidal ideation will be further investigated in the current study using the five-item *Suicidal Ideation Attributes Scale* (SIDAS) [33]. Items on this scale are rated on ten-point scale and assess the frequency of, and control over, suicidal thoughts. Higher scores on the SIDAS are indicative of greater suicidal ideation.

### Suicide risk models

A subsidiary aim of the current study is to explore suicide risk models in an adolescent population to better understand the development and progression of suicidality in young people. The *Interpersonal Needs Questionnaire* (INQ) [34] and the *Acquired Capability for Suicide Scale* (ACSS) [35] will be administered to assess the three constructs (thwarted belongingness, perceived burdensomeness, and acquired capability for suicide) that comprise the Interpersonal Theory of Suicidal Behavior. The INQ contains 15 statements that assess thwarted belongingness (nine items) and perceived burdensomeness (six items). Thwarted belongingness refers to social isolation and broadly comprises loneliness and the absence of reciprocally-caring relationships, while perceived burdensomeness consists of two key dimensions of interpersonal functioning: cognitions of self-hatred and beliefs that one is a liability to others (20). Each item of the INQ is responded to on a seven-point scale ranging from 1 (not at all true for me) to 7 (very true for me). A total scale score for each sub-scale can be calculated by summing individual items for each scale (after reverse coding six items), and a total scale score is calculated by summing these subscale scores. Total scale scores can range from 9 to 63 for thwarted belongingness and 6 to 42 for perceived burdensomeness, with higher scores on each sub-scale indicating higher levels of thwarted belongingness and perceived burdensomeness.

The *Acquired Capability for Suicide Scale* (ACSS) [35] contains seven items that assess fearlessness about death. Each item is responded to on a four-point Likert-type scale ranging from 0 (not at all like me) to 4 (very much like me). Total scale scores are calculated by summing item scores and can range from 0 to 28. Higher scores are representative of greater levels of fearlessness about death.

The relationship between positive future thinking and suicide risk will also be explored through the assessment of *entrapment* [36]. Entrapment will be measured by a four-item scale [17], which was adapted from Gilbert and Allan [36]. Items on this scale are responded to on a five-point scale ranging from ‘not at all like me’ to ‘extremely like me’. Higher scores are suggestive of higher entrapment or a strong motive to take flight that is blocked (e.g. ‘I feel trapped inside myself’).

### Risk and protective factors

A range of putative risk and protective factors will also be measured to be explored as mediators or moderators of intervention effects and for inclusion in models of suicide risk. The factors explored will include self-harm, suicide stigma, suicide literacy, general psychological distress, depressive and anxiety symptoms, bullying, school social inclusion, personality, and risk taking behaviour.

*Self*-*harm* will be measured using three items (yes/no) that assesses the presence of self-injury, whether the intention of the self-injury was to experience pain or suffering and whether the intention of the self-injury was to die.

Suicide stigma will be investigated using the *Stigma of Suicide Scale* (SOSS) [37]. The SOSS contains 16 one or two-word descriptors of people who die by suicide and respondents are asked to rate their level of agreement with each item on a five-point scale ranging from ‘strongly disagree’ to ‘strongly agree’. Higher scores on this scale are suggestive of greater suicide stigma. The *Literacy of Stigma Scale* (LOSS) will also be administered [38] to assess respondent knowledge of the signs and symptoms of suicide, risk factors, and prevention and treatment options. The LOSS consists of 12 items on a ‘true/false/don’t know’ scale. Higher scores are reflective of greater suicide literacy.

General psychological distress will be assessed with the newly developed *Distress Questionnaire Scale* - *5* (DQ5) [39]. This scale contains five items rated on a five-point scale from 1 (never) to 5 (always), with total scores ranging from 5–25. The screener has been shown to be accurate in detecting a range of common mental health problems in community-based settings.

Depressive symptoms will be measured by the *Major Depression Inventory* (MDI) [40]. This scale consists of 12 items (10 questions with 2 sub-items) that cover the ICD-10 and DSM-IV symptoms of depression. These items are rated on a six-point scale from 0 (all the time) to 5 (at no time) with total scale score ranging from of 0 to 50. Higher scores indicate the presence of more depressive symptoms.

Generalised anxiety will be measured using the *Screen for Child Anxiety Related Emotional Disorders GAD subscale* (SCARED-GAD) [41]. The SCARED-GAD consists of nine items rated on a three-point scale ranging from 0 (not true or hardly ever true) to 2 (true or often true). The items included on the questionnaire are reflective of the DSM-IV criteria for generalised anxiety disorder in childhood.

Three items will be used to assess *bullying behaviour* online and in person. The items, which are being used in the current Sources of Strength trial in the USA, are based on questions by Klomek and colleagues [42]. The items enquire how often students have been bullied and how often they have bullied others, on a five-point scale ranging from 1 (not at all) to 5 (most days).

Four items, drawn from the current US Sources of Strength trial, will be used to assess *peer integration at school*, addressing both inclusion and isolation at school (e.g. ‘At my school I feel close to other students’). These items will be rated on a four-point scale ranging from 1 (strongly disagree) to 4 (strongly agree), with higher scores indicating a higher level of social support at school. An additional two items will assess school identification (e.g. ‘I feel a strong connection with my school’) and will be rated on a seven-point scale ranging from 1 (not at all) to 7 (very much).

The *Substance Use Risk Profile Scale* (SURPS-23) [43] will be used to assess the four personality dimensions of hopelessness, anxiety sensitivity, impulsivity and sensation seeking. The SURPS-23 contains 23-items rated on a four-point scale ranging from ‘strongly disagree’ to ‘strongly agree’. The overall score sums to suggest personality risk for substance misuse.

Lastly, risk-taking will be measured using the *Risk*-*Taking and Self*-*Harm Inventory for Adolescents* [44]. This subscale contains eight-items regarding general risk taking behaviours for adolescents, such as classroom cheating, physical fights, excess alcohol consumption, and drug use, which are rated on a four-point scale ranging from ‘never’ to ‘many times’. Higher scores indicate greater participation in risky activities.

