### Statistical analysis

Analyses of continuous measures will be undertaken on an intent-to-treat basis, including all participants randomised regardless of treatment actually received or withdrawal from the study. Mixed-model repeated-measures analyses will be used because of the ability of this approach to include participants with missing data without using biased techniques, such as last observation carried forward [47]. In addition, by incorporating appropriate random effects for schools, this approach can accommodate and assess the magnitude and significance of clustering effects. The primary aim will be evaluated by a contrast examining change in help seeking intentions from pre-intervention to post-intervention in the Sources of Strength condition compared to that in the wait-list control condition. For suicide attempts and other dichotomous outcomes, a comparable binary mixed modelling approach [48] will be used. Differences in relative risk for incidence of suicide attempt from baseline to the 6- and 18-month follow-ups will be assessed. Mediators of intervention outcome including suicidal ideation, depressive symptoms and exposure to school-based messaging will be explored using interaction terms in mixed effects models and using latent class analyses [49]. Models of suicide risk will be developed using regression analyses and structural equation models, testing the Interpersonal Theory of Suicidal Behavior framework and examining the role of additional psychosocial and demographic risk factors. Social network factors will be assessed in a subset of two schools (one control and one intervention), evaluating up to seven connections per student at pre- and post-intervention, to estimate a range of network indices of density, reciprocity, clustering and individual centrality. Change in social network characteristics as a function of intervention condition will be tested. During the messaging phase, engagement with social media messages posted by peer leaders at the intervention schools will be analysed by categorising posts and assessing the types of messaging that best engage students by measuring reach through likes, shares, and comments. This sub-study measures ‘digital footprint’ behaviour, and thus complements the self-report measures of connectivity.

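### The printed MDI item codes run opposite to the stated meaning of the MDI total, and no reversal is given; the ACSS has only a mislabelled number of response points

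*Protocol article*

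**What the plan says.** **MDI (Risk and protective factors).** The article describes the instrument as follows: "This scale consists of 12 items (10 questions with 2 sub-items"). The items cover symptoms of depression, and each is "rated on a six-point scale from 0 (all the time) to 5 (at no time"). The same sentence also gives the range of the sum: "with total scale score ranging from of 0 to 50". The direction is then given: "Higher scores indicate the presence of more depressive symptoms". No reversal of items is mentioned.

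**Use of the MDI.** Table 1 schedules it at all four occasions. Subsidiary aims lists depressive symptoms among the factors for the suicide-risk models and among the predictors and mediators of intervention effects. Statistical analysis names "Mediators of intervention outcome including suicidal ideation, depressive symptoms and exposure to school-based messaging" as variables to be explored, with interaction terms in mixed models as one of the methods.

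**ACSS (Suicide risk models).** The scale "contains seven items that assess fearlessness about death". Each item is answered on a "four-point Likert-type scale ranging from 0 (not at all like me) to 4 (very much like me"). Item scores are summed, and totals "can range from 0 to 28", higher meaning more fearlessness.

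**The concern.** The MDI items are symptoms, so answering that one is present all the time is the most depressed response. The article gives that response the lowest code and then says that high totals mean more depression. A programmer who builds the score from the printed codes and an analyst who reads it from the printed interpretation would each be following the text, and together they would report every MDI relationship backwards. A larger benefit among more depressed students, for example, would be described as a larger benefit among less depressed students.

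The ACSS entry calls for a check as well, because a scale running from 0 to 4 has five points, not four.

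**Working it through.** **Inputs.** MDI: 10 questions, codes 0 to 5, stated total 0 to 50, higher = more symptoms. ACSS: 7 items, codes 0 to 4, simple sum, stated total 0 to 28. All are from the two measure descriptions cited above.

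**Formula.** Range of a summed scale = (number of scored items x lowest code) to (number of scored items x highest code).

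**1. Reproduce the MDI range.** 10 x 0 = 0 and 10 x 5 = 50, so the stated range is right with one score per question. Summing all 12 items would give a maximum of 12 x 5 = 60, so the range requires ten scored questions.

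**2. Check the MDI direction with the extreme respondents.**

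| Respondent | Printed codes | Reversed codes (5 minus item) |
|---|---|---|
| Every symptom all the time | 10 x 0 = 0 | 10 x (5 - 0) = 50 |
| No symptom at any time | 10 x 5 = 50 | 10 x (5 - 5) = 0 |

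Only the right-hand column matches the stated meaning. Both columns span 0 to 50, so checking the range cannot tell them apart.

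**3. Effect on a model.** With all ten questions scored, let M be the score in the intended direction. The score by the printed codes is then M' = 50 - M, which has correlation -1 with M. Take a model with condition T:

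Y = b0 + b1 T + b2 M + b3 T x M

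Substituting M = 50 - M' gives

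Y = (b0 + 50 b2) + (b1 + 50 b3) T - b2 M' - b3 T x M'

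The MDI slope and the MDI-by-condition interaction keep their size and change sign. If the score is not centred, the condition coefficient also moves, because it then refers to the other end of the scale. One quantity would survive: an indirect effect formed as the product of two paths through the MDI is unchanged, since both paths flip, although each path would be misread.

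**4. Check the ACSS.** 7 x 0 = 0 and 7 x 4 = 28, so codes, summing rule and range agree exactly. A true four-point scale would give 0 to 21 if coded 0 to 3 (7 x 3 = 21), or 7 to 28 if coded 1 to 4. Neither is the stated range. The label is therefore the only part that is out of line.

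**The case against.** **The intended direction is clear.** The sentence on interpretation says which way the MDI total should run, so a careful analyst would reverse the items, and nothing is lost because the two scores are exact mirror images. This stands as a limit on the importance of the point. It does not reconcile the two sentences, and nothing elsewhere in the article corrects the codes.

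**A condensed article need not give every scoring step.** The article does mention reversal for six INQ items and for the negatively worded mastery items, but those are subsets of items, so silence on the MDI proves little. It is also uneven elsewhere: the social support responses are listed from often to never, with higher scores meaning more interactions and no reversal stated. This is fair, and the point does not rest on the missing reversal alone. The social support entry prints no numeric codes, so it contradicts nothing. The MDI entry prints codes, range and meaning, and they conflict.

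**The analyses are subsidiary.** This is correct. The primary outcome is the adapted General Help-Seeking Questionnaire, and neither scale enters the sample size. The at-risk procedure is described in terms of reported suicidality, so no consequence for it is shown.

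**A stronger reading of the ACSS is tempting.** A reader might infer from the four-point label that the ACSS is mis-scored too, with a maximum of 21 in place of 28, a range shorter by (28 - 21)/28 = 25%. The documents do not support this. It needs a form with four options coded 0 to 3, against the printed codes, and nothing shows that such a form exists.

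**Conclusion.** The point holds for one variable. As printed, the MDI coding and the MDI interpretation contradict each other. Following the codes while reading the total as stated reverses the scale completely, and with it the sign of the MDI slopes and MDI-by-condition interactions in the exploratory mediator, predictor and suicide-risk analyses.

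This rests on two assumptions: that one score is counted for each of the 10 questions, as the 0 to 50 range requires, and that the score is built from the printed codes. The text does not show that the trial's forms or scoring code carry the error; the anchors may simply be a slip in the article. A reader should not infer that MDI data have been mis-scored, or that any confirmatory result is at risk.

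For the ACSS, scoring by the printed codes gives the stated range and direction. Only the number of points in its label is wrong.

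**What to change.** - **MDI text.** Print the codes as 5 (all the time) to 0 (at no time), or keep the present codes and add that each item is reversed (5 minus item) before summing. State that one score is counted for each of the 10 questions, so that the total is 0 to 50.
- **MDI forms and code.** Compare the online form, the paper form and the scoring code with the corrected text before any MDI analysis. Scoring the two extreme respondents is enough: every symptom all the time must give 50 and no symptom must give 0. Reconcile the item count at the same time, since Table 1 lists 13 MDI items and the description gives 12.
- **ACSS text.** Change the label from four-point to five-point. The codes and range stay as they are.

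The cost is two lines of text and a short check of forms and code. If data have already been collected with the MDI reversed, rescoring recovers them in full.

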### Social network variables

A number of measures, developed specifically for this trial, will also be included to measure social networks and Sources of Strength intervention effects through these networks. These include the following:*Number of friends* – Assessing the number of close friends at school and online (three items)*Number of trusted adults* – Assessing the number of trusted adults at school and outside of school (two items)*Naming trusted adults* – Listing the names of seven adults whom students would ask for help for a suicidal friend*Naming close friends* – A sub-set of students will be invited to list up to seven of their closest friends, how likely they are to seek help from these friends, and how much they are influenced by them, which will be included in a social network analysis.

### Intervention engagement

*Intervention reach* will be measured by 11 questions (e.g. ‘Have you seen a presentation or assembly about strengths that help teens get through hard times?’). The peer leader groups in the intervention schools will additionally be asked six questions assessing the *fidelity* of the intervention. Example items include whether students held regular peer leader group meetings, and whether the peer groups organised any sources of strength activities. School staff in intervention schools will also be invited to participate in a short survey to assess the reach of the whole school messaging and youth-adult connections.

### Sample size and power calculations

Calculation of required sample size was based on detecting a post-intervention effect size of 0.33. This reflects the universal nature of this intervention and is based on effect sizes obtained in the US evaluation of the program [10]. Power was set at 0.8, α = .05 (two-tailed), and correlation of .5 assumed between baseline and endpoint scores. To allow for possible clustering effects (participants from the same school having characteristics and outcomes more alike than between schools), a design effect [45] was calculated to be 12.96, assuming an intraclass correlation (ICC) of 0.04 and an average school size of 300 students. The estimate of the ICC reflects previous Australian school-based studies that have found non-significant intraclass correlations (ICC = .02) [46] and from the US trial ICC = .04 [10]. Accommodating a 20 % attrition rate [46], the target sample size is set at 4,800 or 2,400 students across eight schools per condition.

### Statistical analysis

Analyses of continuous measures will be undertaken on an intent-to-treat basis, including all participants randomised regardless of treatment actually received or withdrawal from the study. Mixed-model repeated-measures analyses will be used because of the ability of this approach to include participants with missing data without using biased techniques, such as last observation carried forward [47]. In addition, by incorporating appropriate random effects for schools, this approach can accommodate and assess the magnitude and significance of clustering effects. The primary aim will be evaluated by a contrast examining change in help seeking intentions from pre-intervention to post-intervention in the Sources of Strength condition compared to that in the wait-list control condition. For suicide attempts and other dichotomous outcomes, a comparable binary mixed modelling approach [48] will be used. Differences in relative risk for incidence of suicide attempt from baseline to the 6- and 18-month follow-ups will be assessed. Mediators of intervention outcome including suicidal ideation, depressive symptoms and exposure to school-based messaging will be explored using interaction terms in mixed effects models and using latent class analyses [49]. Models of suicide risk will be developed using regression analyses and structural equation models, testing the Interpersonal Theory of Suicidal Behavior framework and examining the role of additional psychosocial and demographic risk factors. Social network factors will be assessed in a subset of two schools (one control and one intervention), evaluating up to seven connections per student at pre- and post-intervention, to estimate a range of network indices of density, reciprocity, clustering and individual centrality. Change in social network characteristics as a function of intervention condition will be tested. During the messaging phase, engagement with social media messages posted by peer leaders at the intervention schools will be analysed by categorising posts and assessing the types of messaging that best engage students by measuring reach through likes, shares, and comments. This sub-study measures ‘digital footprint’ behaviour, and thus complements the self-report measures of connectivity.

Given the broad scope of research questions and the incremental availability of data, the publication plan for the study is to examine the help-seeking outcomes, coping/suicidality outcomes, theoretical models, and social network analyses in separate publications. The primary report will be of post-intervention and 6-month follow-up outcomes, with subsidiary analyses to be conducted at the 18-month follow-up to investigate long-term outcomes for the second year of the program.

